### BMI

BMI was calculated using the standard equation (weight [kg]/height[m]^2^). Height was measured to 0.1 cm using the stretch stature method on 0 a stadiometer (Veeder-Root (VR) High Speed Counter) (Harpenden/Holtain, Mentone Education Centre, Morrabin, Victoria). Height was measured twice, with accepted values within 0.3 cm. A third measure was taken if measurements were outside the acceptable range. The average of the two acceptable measures will be reported.

### Waist circumference

Waist circumference was measured at two points: (i) level with the umbilicus, and (ii) at the largest circumference between the lower costal border and the umbilicus. Two measures were taken at each site, with accepted values within 0.5 cm. Further measures were taken if measurements were outside the acceptable range. The average of the two acceptable measures will be reported. To ensure follow up measurements were taken from the same location, the distances between the sternal notch and both waist circumference points were recorded. Each measurement was recorded with a non-extensible steel tape (KDSF10-02, KDS Corporation, Osaka, Japan). This measure will be taken at each time point by one of two assessors with Level 1 Anthropometry qualifications to improve reliability.

### Blood Pressure and Resting Heart Rate

Blood pressure and resting heart rate were measured using NISSEI/DS-105E digital electronic blood pressure monitors (Nihon Seimitsu Sokki Co. Ltd., Gunma, Japan) under standardised procedures. Participants were seated for five minutes before the first blood pressure measurement and a rest period of two minutes between measures was used. Blood pressure was measured three times. Further measurements were taken if the blood pressure or resting heart rate values fell outside of the acceptable ranges i.e. Systolic within 10 mmHg, diastolic within 10 mmHg (preferably 5 mmHg) and resting heart rate within 5 bpm. The mean of the two closest systolic pressures and the diastolic pressure paired to them will be reported. The mean of the two lowest resting pulse pressures will be used.

### Body composition

Bioimpedance was used for the assessment of body composition, including fat mass, fat free mass and total body water. Body composition was assessed by the InBody720 (Biospace Co., Ltd, Seoul, Korea), a multi-frequency bioimpedance device featuring an eight-point tactile electrode system. This device has been shown to be a valid and reliable device for body composition assessment [35,36].

### Physical activity

Physical activity was objectively measured using pedometers (Yamax SW200 pedometers (Yamax Corporation, Kumamoto City, Japan). Participants were sent pedometers in the mail 1-2 weeks prior to the baseline assessment and will be provided with the pedometer at follow-up assessments. Participants were instructed on how to attach the pedometers (at the waist on the right hand side) and asked to remove the pedometers only when sleeping, when the pedometer might get wet (e.g. swimming, showering) or during contact sports. Participants were asked to wear the pedometers for seven consecutive days and keep to their normal routine. At the end of the day participants were instructed to record their steps on a pedometer record sheet and reset their pedometers to zero. Participants were instructed to note down if they did an activity like cycling, swimming, contact sports or another activity that does not involve stepping and include details (type of activity and duration), or if they forgot to wear their pedometer. Participants will be included in all analyses if they have completed at least four weekdays of pedometer monitoring. The average of existing days will be imputed for participants who have included at least four days of data.

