**Figure 1 F1:**
[figure not shown]
**CONSORT Flowchart describing the progress of participants through the trial**.

**Table 1 T1:** Inclusion and exclusion criteria for the SHED-IT community trial

*Inclusion criteria*	*Exclusion criteria*
* were male;	* had a history of major medical problems such as heart disease or diabetes in the last five years that would prevent them from exercising;
* had a BMI between 25 and 40 (kg/m^2^);	* had orthopaedic or joint problems that would be a barrier to physical activity such as walking;
* agreed to not participate in other weight loss programs during the study;	* had recently lost 5% or more of their body weight;
* passed a health-screening questionnaire and a pre-exercise risk assessment [28];	* were taking medications that are affected by weight loss or had resulted in weight gain or loss in the last 3 months;
* were available for assessment sessions;	* were currently participating in an alternative weight loss program.
* had access to a computer with e-mail and Internet facilities;	
* owned a mobile phone.	

(i) SHED-IT *Resources*

(ii) SHED-IT *Online *- Resources plus Internet

(iii) *Wait-list Control - *6 month wait-list

The design, conduct and reporting of this study will adhere to the Consolidated Standards of Reporting Trials (CONSORT) guidelines [27].

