#### (i) SHED-IT Resources

Participants randomised to this group were provided with a weight loss resource package, which included:

- a 25-minute SHED-IT DVD presentation on weight loss for men;

- the SHED-IT *Weight Loss Handbook for Blokes (NB: 'Blokes' is Australian vernacular meaning men)*;

- the SHED-IT *Weight Loss Support Book for Blokes;*

- a pedometer, tape measure for waist circumference measurement and a kilojoule (kJ) counter book.

The SHED-IT resources have been tailored for men, based on our pilot process evaluation [26] and include examples and scenarios that men can relate to and commonly experience. Both the DVD and *SHED-IT Weight Loss Handbook for Blokes *include basic weight loss information (energy balance, calculating total energy expenditure and tracking energy intake) and outline nine key weight loss messages tailored for men. Through the handbook, men are instructed: to measure and record their weight (in kg) and their waist circumference (in cm) once each week; to complete daily eating and exercise diaries for four days each week (including 2 weekdays and 2 weekend days); to record their step counts for four days each week (including 2 weekdays and 2 weekend days); and to identify and record sources of social support; and personal weight, physical activity and eating goals each month for 3 months. The *SHED-IT Weight Loss Support Book for Blokes *contains instructions for calculating both resting metabolic rate and total kJ expenditure; how to plot weight loss, waist circumference loss and weekly average step charts for recording and monitoring progress; space for recording body weight, physical activity and eating goals; space for recording social support strategies; and a daily food and exercise diary to complete.

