#### (iii)Wait-list control

Men randomised to the control group received no intervention and will be required to attend the assessments at baseline, 3- and 6-month follow up. At the 6-month assessments, these men will then be re-randomised to one of the weight loss groups (*Resources *or *Online*).

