### Outcomes

Outcome measures were obtained from all participants at baseline (September, 2010) and will be taken at 3 months (December, 2010), and 6 months (March, 2010) after the start of treatment. The primary endpoint will be based on the 6-month follow up measurement. All measurements will be taken in the Human Performance Laboratory at the University of Newcastle (Australia) using the same instruments at each time point. Trained research assistants will adhere to standardised procedures for all data collection and data will be collected in the same order for each time point measurement. Participants were blind to group allocation at the baseline assessment. Assessors will be blinded to treatment allocation at all time points. Participants allocated to the *Control *group will be asked to return to the University for one further assessment, three months after beginning their weight loss programs (9 months after the beginning of the study).

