### Allocation

Study information for the three different groups was pre-packed into identical black plastic opaque envelopes and consecutively numbered within the three BMI categories and ordered according to the randomisation schedule. The packing and sequencing of these envelopes was completed by a research assistant who was not involved in enrolment, assessment or allocation of participants. Study participants completed all baseline assessments before proceeding to a separate room to meet with a research assistant who was not involved with the baseline assessments. The allocation sequence was concealed during this process. Participants' BMI category was calculated from the baseline measurements and the participant was allocated the next available number in that BMI category before being provided with their information pack. At this point the envelope was opened by the research assistant and details of the particular information pack were provided to the participant using a standardised protocol.

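### As written, the Control group's 6-month pedometer week follows re-randomisation and probably falls in the first week of an active programme

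*Protocol article*

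**What the plan says.** Three sections of the protocol article fix the timing.

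- **Physical activity.** On supply of the device: "Participants were sent pedometers in the mail 1-2 weeks prior to the baseline assessment and will be provided with the pedometer at follow-up assessments". On the record itself: "Participants were asked to wear the pedometers for seven consecutive days and keep to their normal routine".
- **Wait-list control.** "At the 6-month assessments, these men will then be re-randomised to one of the weight loss groups", meaning Resources or Online. The list of study arms agrees, describing the Control arm as a "6 month wait-list".
- **Outcomes.** Control men return for one further assessment, "three months after beginning their weight loss programs (9 months after the beginning of the study").

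The SHED-IT Resources section shows what these men then receive. The package includes "a pedometer, tape measure for waist circumference measurement and a kilojoule (kJ) counter book", and the handbook instructs men "to record their step counts for four days each week (including 2 weekdays and 2 weekend days"). The Online arm gets the same materials plus the website.

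Hypothesis 1(b) claims improvement over Control in secondary outcomes at both 3 and 6 months. The Statistical methods section applies models like the primary one to the other outcomes and names physical activity among those meant to support the primary result.

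**The concern.** A wait-list comparison at 6 months needs the Control value to be an untreated one. Most measurements are taken at the visit, before anything new need happen to the participant. Pedometer steps differ because they take a week to collect. It therefore matters on which side of the visit that week lies, and for Control men at 6 months the visit is also the point of entry to treatment.

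The programme they enter acts directly on this outcome: it supplies a pedometer, asks for step counts and sets physical activity goals. A man in his first week of it is unlikely to be keeping to his normal routine, as the measurement instructions require. Pedometer steps are also the only objective measure of physical activity that the article describes. At stake is whether the 6-month step contrasts against Control still compare treated with untreated men.

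**Working it through.** The article states no planned figure for steps. Its sample size (36 per group, 150 in total) is for weight and plays no part here. The check consists of placing the stated timings side by side and following them through the model.

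**Step 1: where the step week lies.**

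| Visit | Device supplied | Seven-day record |
|---|---|---|
| Baseline | By mail, 1-2 weeks before | Can be complete before the visit |
| 3 and 6 months | At the assessment | Can only follow the assessment |

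The sentence contrasts the two procedures, so it is natural to read the follow-up arrangement as deliberately different from baseline.

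**Step 2: when Control men start treatment.** The extra Control assessment is 9 months after study start and 3 months after programme start:

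9 − 3 = month 6.

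This matches the 6-month wait-list and re-randomisation at the 6-month assessments.

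**Step 3: overlap.** If device and programme materials are both issued at the 6-month visit, the record covers roughly days 0 to 7 of the programme. The article does not give the day on which re-randomised men receive their packs. The nearest evidence is the initial allocation, where the pack was handed over at the visit: "At this point the envelope was opened by the research assistant and details of the particular information pack were provided to the participant". No section holds materials back until the step record is returned.

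**Step 4: effect on the contrasts.** Let I and C be mean steps in an intervention arm and in untreated Control, with subscripts for month. The group-by-6-month term targets

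D = (I₆ − I₀) − (C₆ − C₀).

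If starting the programme raises Control steps in that week by u, then C₆ becomes C₆ + u and the estimate targets

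D − u.

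With D and u both positive and u no larger than D, the contrast shrinks toward zero by u. With u = 0 there is no bias. The article gives neither u nor a step effect or standard deviation, so neither the bias nor any loss of power can be computed.

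**Step 5: what is not touched.**
- *Weight and other measures taken at the visit*: they do not depend on the week that follows.
- *3-month step contrasts*: Control men are still waiting. The planned model has a separate group-by-time term for each visit, so a common shift in the Control 6-month value enters only the 6-month term.
- *Online versus Resources*: fitted as a separate pairwise model without Control data.

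**The case against.** The strongest reply is that the overlap is inferred. The article uses the word assessments for whole measurement rounds, so a pedometer provided at follow-up assessments could mean provided in each round, possibly ahead of the weight visit. Re-randomisation is likewise placed in a round, not in a sequence within it. The 9 − 3 arithmetic works in months and cannot by itself place a seven-day window. At baseline all assessments were finished before allocation; the same order at 6 months, with the step record counted as an assessment, would remove the problem. Day-level logistics are also something that a journal article may leave to the full protocol.

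Much of this stands. A reader might infer that the article states that Control steps are recorded on treatment; it does not. The round-wide reading is possible, but it has to set aside the contrast with mailing at baseline, and no section places the Control step week before re-randomisation. The point concerns how the stated timings combine, not a missing detail.

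Two further limits also stand. Baseline and follow-up weeks lie on opposite sides of the visit in every arm, so that difference does not by itself bias a between-group contrast. And men are told to keep to their normal routine during the wear week, so the uplift could be small.

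**Conclusion.** The point holds as a conditional one of moderate severity. Followed as written, and unless materials are held back, the plan records the Control group's 6-month steps in the first week of an active programme. The two 6-month step contrasts against Control are then probably biased toward no difference. This rests on three assumptions: the follow-up device is issued at the visit itself, re-randomised men receive their materials at about that time, and starting the programme raises steps. The first is the plainest reading of the text, the second is supported only by the initial allocation procedure, and the third is plausible given the programme content. The size is unknown.

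A reader might infer that the trial's primary comparison is compromised, because 6 months is the primary time point. The documents do not support that: the primary outcome is weight, measured at the visit, and its analysis and multiplicity control are unaffected. Steps are a secondary outcome, and their 3-month comparison keeps an untreated Control.

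**What to change.** For follow-up, and at least for the 6-month visit in all arms, mail the pedometer and record sheet 1-2 weeks before the appointment, as at baseline. Collect the completed sheet at the visit, before Control men are re-randomised and before any programme materials are released. Using the same procedure in every arm keeps the measurement comparable between groups.

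Reconcile the Physical activity, Wait-list control and Outcomes sections so that they state this order. If the intended procedure already places the step week before re-randomisation, stating so is enough.

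If any 6-month Control step data are nevertheless recorded after re-randomisation, flag them and treat the 3-month contrast as the untreated-control comparison for steps. A blanket exclusion is not advisable, since it could remove the whole Control arm from the 6-month contrast.

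The cost is postage and a few lost or forgotten devices. The trial has already used this procedure at baseline. The change has to be made before the 6-month visits, because an untreated Control step week cannot be recovered afterwards.

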### Dietary Intake

Dietary intake was assessed using the Australian Eating Survey (AES). AES is a 120-item semi-quantitative Food Frequency Questionnaire (FFQ), used previously in Australian youth up to 16 years [37] and currently being validated in both adult males and females. Portion sizes for individual food items were generated by the Australian Bureau of Statistics (ABS) [38] and unpublished data from the 1995 Australian National Nutrition Survey; or the "natural" serving size for common items such as a slice of bread. Subjects were asked about frequency of their consumption over the previous six months with frequency options ranging from 'Never' up to '4 or more times per day' but varying depending on the food item. Twenty-one questions related directly to the intake of vegetables and 11 questions related to fruit. Seasonal availability of some fruits will be considered in the nutrient analysis.

Nutrient intakes from the AES will be computed from the most current food composition database of Australian foods available, the Australian AusNut 1999 database (All Foods) Revision 17 and AusFoods (Brands) Revision 5 (Australian Government Publishing Service, Canberra) to generate individual mean daily macro-and micro-nutrient intakes. The AES includes questions about the total number of daily serves of fruit, vegetables, bread, dairy products, eggs, fat spreads, sweetened beverages and snack foods, as well as asking the type of bread, dairy products and fat spreads used. Twelve questions relate to food-related behaviours, including items on frequency of take-away food consumption and eating while watching television.

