**Methods and Design:**

The study design is an assessor blinded, parallel-group randomised controlled trial that recruited 159 overweight and obese men in Newcastle, Australia. Inclusion criteria included: BMI 25-40 (kg/m^2^); no participation in other weight loss programs during the study; pass a health-screening questionnaire and pre-exercise risk assessment; available for assessment sessions; access to a computer with e-mail and Internet facilities; and own a mobile phone. Men were recruited to the SHED-IT (Self-Help, Exercise and Diet using Internet Technology) study via the media and emails sent to male dominated workplaces. Men were stratified by BMI category (overweight, obese class I, obese class II) and randomised to one of three groups: (1) SHED-IT *Resources *- provision of materials (DVD, handbooks, pedometer, tape measure) with embedded behaviour change strategies to support weight loss; (2) SHED-IT *Online *- same materials as SHED-IT *Resources *plus access to and instruction on how to use the study website; (3) Wait-list Control. The intervention programs are three months long with outcome measures taken by assessors blinded to group allocation at baseline, and 3- and 6-months post baseline. Outcome measures include: weight (primary outcome), % body fat, waist circumference, blood pressure, resting heart rate, objectively measured physical activity, self-reported dietary intake, sedentary behaviour, physical activity and dietary cognitions, sleepiness, quality of life, and perceived sexual health. Generalised linear mixed models will be used to assess all outcomes for the impact of group (*Resources*, *Online*, and *Control*), time (treated as categorical with levels baseline, 3-months and 6-months) and the group-by-time interaction. These three terms will form the base model. 'Intention-to-treat' analysis will include all randomised participants.

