### Aims And Hypotheses

Our overall research question is: *Can relatively low dose weight loss programs be effective in achieving weight loss in a community sample of overweight men? *The primary aim is to determine the efficacy of two behavioural weight loss programs designed to be incremental in the extent of interaction and intensity of participation, and differ in mode of delivery in a large community trial. A secondary aim is to compare the effectiveness of the different intervention programs in defined subgroups (e.g., age, education, occupation, marital status, SES).

It is hypothesised that:

(1) Compared to the Wait-list Control, both the SHED-IT *Resources *and *Online *interventions will result in a clinically important and statistically significant (a) reduction in weight and (b) improvement in other important secondary outcomes at 3 and 6 months post-baseline

(2) The SHED-IT *Online *program will result in greater improvements in the primary and secondary outcomes at 3 and 6 months post-baseline compared to the SHED-IT *Resources *program.

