### Statistical methods

Analyses will be performed using Stata Version 11 or later. All variables will be checked for plausibility and missing values. Data will be presented as mean (sd) for continuous variables and counts (percentages) for categorical variables. Differences between groups at randomisation and characteristics of completers versus dropouts will be tested using independent *t *tests for continuous variables and chi-squared (χ^2^) tests for categorical variables. The significance level for the comparison of baseline characteristics will be set at 0.05.

A series of Generalised Linear Mixed Models (GLMMs) with a random intercept for individual will be used to test for differences between treatment groups in the mean level of weight after treatment. Separate models will be fit for each of the pair-wise comparisons (*Resources *vs. *Control*; *Online *vs. *Control*; and *Resources *vs. *Online*). The independent variables in the model will include a variable for treatment group, time (treated as categorical with levels baseline, 3-months and 6-months) and the group-by-time interaction. The model will also include a term for the stratifying variable of BMI group at baseline. The coefficient and p-value for the group-by-6 month interaction term will be used to determine the efficacy of the interventions. Similar models will be used to examine differences in change in other outcome measures.

Using the same approach, additional exploratory models will be used to examine subgroups of the study population. These models will contain the variable that identifies the subgroup (such as SES) and of interest will be the 3 way interaction of treatment group by time by SES. We will also examine a range of secondary outcomes to support the primary outcome (e.g. reduction in waist circumference, increase in physical activity, reduction in kilojoule intake). Additional exploratory models will be fitted to examine if the men who have the greatest reduction in weight are also those who have the greatest improvements in the secondary outcomes.

Statistical significance of the primary efficacy analysis (3 pair-wise comparisons) will be based on Hochberg's multiple testing procedure with the family wise error rate held at 5%. All secondary hypothesis tests will be performed using a 2-sided 5% significance level. In addition, linear regression and GLMMs will be used to describe relationships among the various dependent and independent variables.

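### At the 3-month visit, half of the six-month dietary recall window precedes randomisation, so the 3-month dietary contrast is biased toward no effect

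*Protocol article*

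**What the plan says.** Under Dietary Intake, the protocol article describes the AES as a 120-item food-frequency questionnaire with a six-month reference period: "Subjects were asked about frequency of their consumption over the previous six months". The same section says the survey was previously used in young people up to 16 years and is still being validated in adults.

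Under Outcomes, the schedule is fixed: "Outcome measures were obtained from all participants at baseline (September, 2010) and will be taken at 3 months (December, 2010"), with a further assessment at 6 months. Measurements are made "using the same instruments at each time point". No different reference period is given for follow-up.

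Under Allocation, group assignment follows directly on the baseline visit: "Study participants completed all baseline assessments before proceeding to a separate room to meet with a research assistant", who then opened the allocation envelope. The abstract adds that "The intervention programs are three months long", so the 3-month visit is the end-of-programme assessment.

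Aims And Hypotheses expects, for both programs against control, "improvement in other important secondary outcomes at 3 and 6 months post-baseline", and hypothesis 2 names the same two times for Online against Resources. Statistical methods lists among the secondary outcomes meant to support the primary one "reduction in waist circumference, increase in physical activity, reduction in kilojoule intake". Secondary tests use a two-sided 5% level.

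**The concern.** Visits are three months apart, but the questionnaire looks back six months. At month 3 a respondent who follows the instruction is averaging his diet over three months when nobody was treated and three months when two of the three arms were. Randomisation makes the arms equal in expectation over the first half, so that half contributes no expected difference and shrinks the contrast. Randomisation does not remove the problem, because this is attenuation and not confounding.

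At stake is the reading of the end-of-programme dietary result. Eating behaviour is one of the main targets of both programs. A small or non-significant 3-month difference in kilojoule intake could be taken as evidence that the programs did not change diet, when part of the shortfall comes from the reference period.

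**Working it through.** The protocol states no dietary effect size, standard deviation or power, so there is no figure of its own to reproduce. The check is of the window against the schedule.

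**Inputs from the protocol article**
- Recall window W = 6 months (Dietary Intake).
- Visits at t = 0, 3 and 6 months, same instruments (Outcomes).
- Allocation directly after baseline, so t = 0 divides untreated from treated diet (Allocation).
- Two-sided 5% level for secondary tests (Statistical methods).

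**Step 1: share of the window after randomisation.** Share = min(t, W)/W.
- Month 3: 3/6 = 50% after, 50% before.
- Month 6: 6/6 = 100% after, none before.

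This step needs no assumption beyond the same reference period being used at follow-up.

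**Step 2: effect retained at month 3, even recall, immediate and constant change.** Retained = (3 × 0 + 3 × 1)/6 = 50%.

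**Step 3: recall weighted to recent months.** Assume exponential weights with half-life h months and an immediate, constant change. Retained = (1 − 2^(−3/h))/(1 − 2^(−6/h)) = 1/(1 + 2^(−3/h)).

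| Half-life h (assumed) | Retained |
|---|---|
| 6 months | 59% |
| 3 months | 67% |
| 2 months | 74% |
| 1 month | 89% |

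**Step 4: gradual onset, even recall.** Assume the effect builds linearly over r months and then holds. As a share of the effect reached at month 3, retained = ((3 − r) + r/2)/6.

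| Build-up r (assumed) | Six-month window | Three-month window, for comparison |
|---|---|---|
| 1 month | 2.5/6 = 42% | 2.5/3 = 83% |
| 2 months | 2/6 = 33% | 2/3 = 67% |
| 3 months | 1.5/6 = 25% | 1.5/3 = 50% |

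The last column separates two things. Any retrospective average falls short of an effect that is still building. The overlap with the untreated period then halves whatever is left, as long as recall is even.

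**Step 5: what this does to a test, as illustration only.** Take an effect that would have 80% power undiluted. With a fraction f retained, power ≈ Φ(f × (1.960 + 0.842) − 1.960), ignoring the negligible opposite tail.
- f = 0.75: Φ(0.141) = 56%.
- f = 0.50: Φ(−0.559) = 29%.

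At 36 men per arm (the number in the Sample size section), 80% undiluted corresponds to a standardised difference of about 0.67. That value is solved for and does not come from the protocol. With about 53 per arm (159 recruited / 3, ignoring attrition), a two-sample t-test for the same 0.67 has 93% power undiluted and 40% at half.

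**The case against.** The strongest reply is that only the calendar overlap is established. How men weight the months, and how fast diet changed, are not in the document. A reader might infer that the 3-month effect is halved as a matter of fact, or that the questionnaire cannot show an end-of-programme change. Neither is supported: 50% is one scenario in a range of roughly 25% to 89%, and lower power is not inability to detect. The 29% figure likewise rests on an effect size chosen to give 80% power at 36 per arm, and on a simple two-group comparison where the protocol plans a mixed model. These objections stand, and the power figures should be read as illustration.

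The reach is also limited. Diet is one of many secondary outcomes. The primary endpoint is weight at 6 months. Statistical methods judges efficacy on the group-by-6-month term and uses similar models for other outcomes, and at 6 months the window is wholly after randomisation. The error is toward the null and cannot create a spurious benefit. A reader might also infer that the 3-to-6-month dietary trend is distorted, since the two windows share three months, but the protocol names no such contrast for diet. All this bounds the point. It does not remove it, because the hypotheses still name 3 months.

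Last, the recall wording is in the past tense in an article written after baseline, and the follow-up form is not shown. Carry-over is inferred from the same-instruments statement. It is the likelier reading, and nothing in the article points to a shorter period at follow-up.

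**Conclusion.** The point holds. As the protocol is written, half of the 3-month AES window precedes randomisation, and the 3-month between-group dietary difference is biased toward zero. The direction rests on the six-month period being used at follow-up and on the arms being alike in diet before allocation, which randomisation provides in expectation. The size is uncertain: about 50% of the effect is retained under even recall and an immediate, constant change, about 59% to 89% under the recency weightings tried, and about 42% to 25% of the month-3 effect under gradual onset with even recall.

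The problem is confined to the AES outcomes at 3 months. The weight analysis is untouched. The 6-month dietary contrast has no untreated period in its window, although it averages the three programme months with the three months after. A null 3-month dietary result should not be read as absence of dietary change during the programme.

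**What to change.** State in the analysis plan that the dietary conclusions for hypotheses 1(b) and 2 rest on the 6-month AES contrast. Report the 3-month AES contrast with its interval as attenuated and descriptive, with a sentence explaining that half of its recall window precedes randomisation, and do not present it as a test of end-of-programme dietary change. This needs no new data and sits close to the 6-month emphasis already in Statistical methods. Its cost is that the trial gives up a formal dietary test at the end of the programme.

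If the 3-month wave has not yet been collected, an alternative is to set the reference period at that visit alone to the three months since baseline, in all three arms. The post-randomisation share then rises from 3/6 = 50% to 3/3 = 100%. The cost is that within-arm change from baseline is no longer like for like, and the wording departs both from the same-instruments rule and from the form being validated in adults. The between-group comparison is preserved because the wording is common to all arms.

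Leave the 6-month questionnaire unchanged. Its window is already wholly after randomisation, and shortening it would change what is measured to the post-programme months only.
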